### Statistical analysis

Details of all statistical analysis methods relating to the interim and final (stage 2) analyses will be documented in an open-access and prespecified statistical analysis plan before accessing unblinded data. Interim and final (stage 2) analyses for efficacy will be based on a modified intention-to-treat population—all randomised participants who have outcome data regardless of non-compliance, protocol deviations or withdrawals. Sensitivity analysis will be performed on the per-protocol population—all randomised participants who adhered to treatment with no major protocol deviations. Adherence is defined as completing 40/60 therapy sessions for at least 30 min per session (all groups) and completing at least 1 hour of tVNS with activities of daily living (ADLs). Safety population will include eligible participants with informed consent, and analysis will be based on the treatment they received. Reporting will adhere to the Adaptive Designs Consolidated Standards of Reporting Trials Extension.^24^

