
## Study aims and objectives

The TRanscutaneous lImb reCovEry Post-Stroke (TRICEPS) trial aims to investigate the efficacy and mechanism of tVNS paired with upper limb rehabilitation on arm recovery in chronic stroke. The primary objective is to determine whether tVNS paired with self-delivered home rehabilitation therapy of the affected arm poststroke reduces arm motor impairment at 3 months from the start of treatment compared with self-delivered home rehabilitation therapy alone.

Secondary objectives are to determine: (a) whether the benefits of tVNS and self-delivered home rehabilitation therapy in reducing arm motor impairment observed at 3 months from the start of treatment are sustained; (b) whether tVNS and self-delivered home rehabilitation therapy improve other outcome measures related to sensory modalities, neurological deficit, QoL, depression, general anxiety, fatigue, pain, spasticity, strength and activities of daily living and (c) the safety of tVNS and self-delivered home rehabilitation therapy.

An imaging substudy will explore whether tVNS changes the cerebral representation of the affected arm, cerebral perfusion and functional connectivity and how they relate to reduced arm motor impairment.

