#### Exclusion criteria

Has significant other impairment of the upper limb, for example, a frozen shoulder.Has severe spasticity (eg, as identified by the ULFM).Has other health conditions that prevent engagement with rehabilitation therapy, for example, advanced dementia.Has severe aphasia and either: (a) informed consent is unlikely based on the Consent Support Tool, (b) engagement with repetitive task training is difficult or (c) inability to communicate AEs from tVNS.Currently participating in another interventional stroke rehabilitation trial.Pregnant or trying to get pregnant.Has a pacemaker or another implanted electrical device.Has a cochlear implant or other similar device.Is currently receiving therapy or treatment to reduce arm motor impairment and would not be willing to stop for the duration of the trial.Has previously experienced a haemorrhagic stroke.Administration of botulinum toxin in the affected arm within the previous 3 months (participants must also be willing to not have further injections for the duration of the trial).

The entry criteria of a ULFM motor subscore of 20–50 is in line with the VNS-REHAB trial.^6^ This will enable a more direct comparison of the relative efficacy of invasive versus non-invasive VNS. The study team, including a patient and public involvement panel, felt that participants scoring <20 points on the ULFM may struggle to carry out repetitive task practice, thereby limiting the potential for meaningful gains, and those scoring >50 points on the ULFM have less impairment, and thereby the score may have a ceiling effect. The range of 20–50 aims to be as inclusive as possible while acknowledging the possibility of different trajectories of rehabilitation response according to stroke severity.^13^ The inclusion of participants from 6 months to 10 years poststroke is justified by previous work on intensive upper limb rehabilitation and was codesigned in consultation with stroke survivors. Spontaneous biological recovery is a prominent mechanism of recovery in the first 3–6 months poststroke, followed by a more stable chronic deficit.^14^ In the chronic phase (after 6 months), improvements in limb function are driven by rehabilitation, often delivered at high doses.^15 16^ Previous studies of intensive upper limb rehabilitation in stroke have shown improvements even several years poststroke onset.^16^

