### Randomisation

Eligible and consenting participants will be randomised using a centralised, validated, restricted, web-based randomisation system (SCRAM - Sheffield Clinical Trials Research Unit Randomisation System) hosted by the University of Sheffield Clinical Trials Research Unit (CTRU). Participants will be randomised 1:1:1 to one of three treatment groups using minimisation with a masked random probabilistic element to reduce the predictability of treatment allocation. A prespecified number of initial participants will be randomised using simple randomisation after which the randomisation will be minimised according to age (≤60, >60 years), baseline ULFM score (20–35, 36–50) and biological sex at birth (male, female) and by recruiting site to achieve good balance across treatment groups with respect to potential prognostic factors. The allocation ratio will be updated to 1:1, and the minimisation algorithm will be updated if a treatment is dropped at interim analysis.

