### Safety monitoring and reporting

AEs and SAEs are defined as events that occur between randomisation and completion of their 6-month follow-up. These may be identified by the participant, research nurse, therapist or any other individual at any point in the trial. AEs will be recorded on the AE report form within the participant CRF. Some expected AEs include those known to be associated with tVNS and/or rehabilitation, including skin irritation, headache, nausea and limb pain.^25^ In a recent systematic review of auricular tVNS, no adverse cardiac events were reported in 484 212 min-days of stimulation.^26^ SAEs will be reported to the CTRU immediately and within one working day from identification. Unexpected SAEs related to the intervention will be reported to the research ethics committee within 15 working days. AEs and SAEs will be reviewed by the DMEC and TSC regularly.

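### The safety population is defined by eligibility and consent rather than by randomisation and device use, so a treated participant later found ineligible would, as written, be outside the safety analysis but inside the efficacy analysis

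*Protocol article*

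**What the plan says.** All references are to the protocol article.

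- **Safety population** (Statistical analysis): "Safety population will include eligible participants with informed consent, and analysis will be based on the treatment they received". No other definition of this population appears in the article.
- **Efficacy population** (same section), for the interim and final analyses: "all randomised participants who have outcome data regardless of non-compliance, protocol deviations or withdrawals".
- **Entry to the trial** (Randomisation): "Eligible and consenting participants will be randomised using a centralised, validated, restricted, web-based randomisation system".
- **Event collection** (Safety monitoring and reporting): "AEs and SAEs are defined as events that occur between randomisation and completion of their 6-month follow-up". The same section adds: "AEs and SAEs will be reviewed by the DMEC and TSC regularly".
- **Objective** (Study aims and objectives): a secondary objective is to determine "the safety of tVNS and self-delivered home rehabilitation therapy".
- **Exclusions** (Exclusion criteria) include "Has a pacemaker or another implanted electrical device" and "Pregnant or trying to get pregnant".

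**The concern.** A safety population is normally built on exposure: whoever received the intervention is counted, whether or not they should have been enrolled. Here the two stated conditions are eligibility and consent. Neither randomisation nor use of the device is among them.

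The difference matters only for participants randomised in error, but that is the case a population definition has to settle. Some exclusions depend on medical history or on what the participant discloses, and core criteria are first screened by a telephone checklist. A breach could come to light after stimulation has begun. Applied literally, the rule then removes that participant, and any events they had, from the safety tables. The same participant stays in the efficacy comparison if outcome data are available.

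At stake is the completeness of the reported safety results for a self-administered home device, which address a stated secondary objective. The primary endpoint, sample size, type I error and interim selection rule are not involved.

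**Working it through.** The point rests on a definition, so the main check is to set the sections side by side. The arithmetic only gives a sense of scale.

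**1. Comparing the definitions**

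| Set | Randomised? | Eligibility condition? | Other condition |
|---|---|---|---|
| Modified intention-to-treat | yes | none; protocol deviations are kept | outcome data available |
| Per-protocol | yes | none by name; major deviations removed | adherence to treatment |
| Safety | not stated | yes | informed consent |
| AE/SAE collection | yes (starts at randomisation) | none | up to the end of follow-up |

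The safety set is the only analysis population not built from randomised participants, and the only one that names eligibility. Consider a participant who is randomised, uses the device, has a 3-month ULFM score and is then found to have breached an exclusion criterion:

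- Event collection: included.
- Modified intention-to-treat: included.
- Safety population, as worded: not included.

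Nothing elsewhere in the article brings this participant back into the safety population.

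**2. The base number**

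Sample size justification and interim analysis gives 228 evaluable participants (76 per group) and 6% dropout.

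- Total: 228 / (1 − 0.06) = 242.6, rounded up to 243.
- Per group: 76 / (1 − 0.06) = 80.9, rounded up to 81.

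Both agree with the article. They are maxima, since an arm may be dropped at the interim analysis.

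**3. How many participants could be affected**

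The article gives no rate of randomisation in error. Under assumed rates:

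- 1%: 0.01 × 243 = 2.4 in total, 0.8 per group.
- 3%: 0.03 × 243 = 7.3 in total, 2.4 per group.
- 5% (a wider bound): 0.05 × 243 = 12.2 in total, 4.1 per group.

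**4. Effect on an event rate in one group of 81**

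Let x participants out of n have an SAE, and remove one participant.

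- If the removed participant had an SAE, the rate goes from x/n to (x − 1)/(n − 1). With x = 1 and n = 81: 1/81 = 1.23% becomes 0/80 = 0%, a fall of about 1.2 percentage points.
- If the removed participant had no SAE, the rate goes from x/n to x/(n − 1). With x = 1 and n = 81: 1.235% becomes 1/80 = 1.250%, a rise of about 0.015 points.

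The sign of the change therefore depends on who is removed.

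**5. Effect on precision**

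With no events among n participants, the one-sided 95% upper bound for the event risk is 1 − 0.05^(1/n).

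- n = 81: 3.63%.
- n = 77 (four removed, the 5% assumption): 3.82%.

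Loss of precision is negligible. What matters is which participants are left out.

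**The case against.** The strongest reply is that the sentence describes the people the trial means to enrol. It says the population will *include* eligible, consenting participants; it does not say *only* these, and no section describes removing a treated participant. The wording is close to that of the Randomisation section, where eligible and consenting people are those who are randomised. The authors may have meant everyone randomised, analysed as treated. This stands as a plausible account of intent. It does not settle the case in which someone is randomised in error. The efficacy definition in the same section shows that the authors could write that rule plainly.

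A second reply is that the full protocol and the analysis plan may define the set differently. That is possible and limits confidence about what will be done. But the article states a rule rather than leaving one open, and that rule would need to be reconciled with any other version.

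Several stronger readings are tempting, and the document does not support them:

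- **That events would be lost to oversight.** AEs and SAEs are collected from randomisation with no eligibility condition and are reviewed by the DMEC and TSC. Only the final safety analysis is affected.
- **That harm rates would be understated.** Removing a participant changes numerator and denominator together, and the rate can move either way.
- **That those removed are the participants most at risk.** The article explains the ULFM range and the time since stroke, but gives no reasons for the individual exclusions. A safety purpose for the implanted-device or pregnancy criterion is plausible but not stated. Other breaches, such as a baseline score out of range, need carry no extra risk. A pregnancy conceived after randomisation would not by itself make a participant ineligible at entry.
- **That people consented but never randomised would distort the analysis.** They meet the literal wording, but events are counted only from randomisation and they received no treatment, so they add nothing to any group.

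**Conclusion.** The concern holds in a limited form. The stated safety population has an eligibility filter that the efficacy population lacks, and it is not tied to randomisation or device use. Followed as written, a treated participant later found ineligible is left out of the final safety analysis while remaining in the efficacy analysis if outcome data exist.

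The number affected is probably small: about 2 to 7 of up to 243 participants. This rests entirely on an assumed 1% to 3% rate of randomisation in error. The direction of any bias is unknown.

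The severity is moderate. The wording is inconsistent with the rest of the section and bears on a secondary objective, but it does not conceal events during the trial and does not touch the primary analysis.

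**What to change.** Replace the sentence with a definition based on exposure: the safety population comprises all randomised participants who used the device, active or sham, at least once, whether or not they are later found ineligible, analysed by the treatment received. Add that events in randomised participants who never used the device will be listed separately.

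Carry the same wording into the full protocol and the analysis plan, and settle it before unblinded data are accessed for analysis. If those documents already define the set this way, the article only needs to be reconciled with them.

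The cost is one or two sentences. Events are already collected from randomisation and the device already records its use, so no new data are needed. Sample size, power and type I error do not change.

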### Primary outcome

The primary outcome (change in ULFM total motor score at 3 months) will be analysed using a mixed effects linear regression model adjusted for fixed effects covariates (baseline ULFM score, age AND sex) and site (random effect). Treatment effects will be presented as the adjusted mean difference in change with multiplicity-adjusted CIs and associated p values. Subgroup analyses will be undertaken to explore the effect of important variables related to the participant and their treatment on the primary outcome. These subgroups are:

Age (≤6, >60 years).Baseline ULFM score (20–35, 36–50).Biological sex at birth (male, female).Side of hemiparesis (left, right).Time since stroke (<12 months, >12 months).Baseline mNIHSS score (0–4=minor, 5–20=moderate and 21–31=severe).

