### Inclusion and exclusion criteria

#### Inclusion criteria

Aged 18 years or greater.Anterior circulation ischaemic stroke (internal carotid, middle cerebral artery, anterior cerebral artery or anterior circulation lacunar stroke) between 6 months and 10 years previously.Baseline Upper Limb Fugl-Meyer (ULFM) total motor score of 20–50 (inclusive) indicating moderate to severe arm motor impairment.At least 10 degrees of active wrist extension, 10 degrees of active thumb abduction/extension and 10 degrees of active extension in at least two additional digits in the affected arm.Able to participate in active rehabilitation therapy, provide feedback on adverse events (AEs) and give informed consent based on clinical judgement.

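### Optional improvement: the primary model could also adjust for time since stroke, which is known for every participant and may add a little precision

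*Protocol article*

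**What the plan says.** In the protocol article, the Primary outcome section specifies a mixed effects linear regression "adjusted for fixed effects covariates (baseline ULFM score, age AND sex) and site (random effect". The Randomisation section minimises on "age (≤60, >60 years), baseline ULFM score (20–35, 36–50) and biological sex at birth (male, female) and by recruiting site", so the model carries every minimisation factor and nothing else.

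Time since stroke appears in two other places. The Inclusion criteria admit anterior circulation strokes "between 6 months and 10 years previously". The Primary outcome section also lists "Time since stroke (<12 months, >12 months" as a subgroup, under the sentence "Subgroup analyses will be undertaken to explore the effect of important variables related to the participant and their treatment on the primary outcome".

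The text after the Exclusion criteria bears on how much time since stroke might matter: "Spontaneous biological recovery is a prominent mechanism of recovery in the first 3–6 months poststroke, followed by a more stable chronic deficit". It adds: "Previous studies of intensive upper limb rehabilitation in stroke have shown improvements even several years poststroke onset".

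**The concern.** The longest permitted interval is 20 times the shortest (120 months against 6). The value is on record for everyone, because eligibility cannot be judged without it, and the plan already means to use it with the primary outcome. Yet it enters neither the minimisation nor the primary model. Its only use is a split at 12 months, which puts everyone from 1 to 10 years after stroke into one category.

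If time since stroke predicts change in ULFM once baseline ULFM, age, sex and site are accounted for, the part it explains now sits in the residual variance. Prespecified adjustment for a baseline value would remove that part without affecting the type I error rate. What is at stake is some power at the final analysis and a slightly less noisy arm selection at the interim.

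**Working it through.** **Inputs from the article (Sample size justification and interim analysis).** Target difference 3 points; expected SD 5.5; 38 per group at interim and 76 at the end; selection bound 0.792; final critical value 2.176; stated marginal power 85%.

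**Input not in the article.** The partial R² of time since stroke, given the four existing factors. I take 0 to 0.09 as an assumption.

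**Step 1: reproduce the design.**
- Selection bound: 1 / (5.5 × √(2/38)) = 0.7925, which agrees with 0.792 for a 1-point difference.
- Final standard error: 5.5 × √(2/76) = 0.892. Drift: 3 / 0.892 = 3.362.
- Marginal power is P(Z₁ > 0.792 and Z₂ > 2.176), where the two statistics are bivariate normal with correlation √0.5. This gives 86.1%, against the stated 85%.
- Simulated family-wise error (10 million draws, two active arms sharing a control, interim rule binding) is 0.0249, against 0.025.

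The stated design therefore reproduces and meets its power without any further covariate.

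**Step 2: add time since stroke.** Residual SD becomes 5.5 × √(1 − R²). Everything else stays the same.

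| Assumed partial R² | Residual SD | Final SE | Marginal power | Equivalent saving, 228 × R² |
|---|---|---|---|---|
| 0 | 5.500 | 0.892 | 86.1% | 0 |
| 0.01 | 5.472 | 0.888 | 86.4% | about 2 |
| 0.04 | 5.389 | 0.874 | 87.5% | about 9 |
| 0.09 | 5.247 | 0.851 | 89.2% | about 21 |

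**Step 3: price of the extra term.** With about 220 residual degrees of freedom, the standard error changes by a factor of about √[(1 − R²)(1 + 1/220)]. This equals 1 at R² = 1/221, or about 0.005. Above that the term pays for itself. At R² = 0 the loss is about 0.2% of the standard error.

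**Step 4: sensitivity to the starting SD.** The article states no reduction of the 5.5 for covariates. If the existing covariates already explained 20% of the variance (an assumption), the SD would be 5.5 × √0.8 = 4.919 and power would already be 92.8%. Time since stroke at R² of 0.01, 0.04 or 0.09 would then bring it to 93.0%, 93.7% or about 94.8%. That is a gain of roughly 0.2 to 2 points.

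**Step 5: the bounds.** If the variance falls by the same factor at both stages, the information fraction stays at one half and the correlation at √0.5. The 0.792 and 2.176 bounds therefore need no change.

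**The case against.** The strongest reply is that nothing here is wrong. Analysing on the factors used in the minimisation is a complete and coherent specification, the comparison is unbiased under randomisation, and the stated power is met. All of that stands.

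A reader might infer three stronger things, and the article supports none of them.

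- *That precision is definitely being lost.* This needs a prognostic effect, which the article nowhere states. A wide eligibility range describes the spread of the covariate, not the outcome variance it explains. The wording about important variables introduces an exploratory subgroup list, which also holds side of hemiparesis and baseline mNIHSS, and both of those are outside the model too. The article's description of the chronic phase points to a weak relation: the 6-month entry limit leaves out the period of prominent spontaneous recovery, and late improvement is reported. It does not go so far as to say that response is unrelated to time since stroke.

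- *That chance imbalance threatens the interim selection.* At R² = 0.04, one SD of the covariate is worth 0.2 × 5.5 = 1.1 points. The between-arm imbalance has standard error √(2/38) = 0.229 SD, so an imbalance of two standard errors would move the estimate by 2 × 0.229 × 1.1 = 0.5 points. But this component is (1.1 × 0.229)² = 0.064 of an interim variance of 5.5² × 2/38 = 1.592, which is the same 4%. The standard error and the stated error rate already include it. Adjustment would reduce noise, not remove a bias.

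- *That the randomisation falls short.* Minimisation is there for "recruiting site to achieve good balance across treatment groups with respect to potential prognostic factors". The article does not have to balance every candidate factor, and I do not suggest altering the algorithm.

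It is also fair to say that the article leaves full detail to a separate statistical analysis plan, which may already contain further adjusted analyses, and that it does not show whether the interim has taken place.

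**Conclusion.** This is a free improvement and not an error. The primary model is valid as written, and omitting time since stroke may give up some precision. Under an assumed partial R² of 0 to 0.09, marginal power would go from 86.1% to between 86.1% and about 89.2%, and the gain is smaller in absolute terms if the existing covariates already bring the SD below 5.5. Given the article's view of the chronic phase, the lower part of that range is the more plausible. The suggestion is worth making because the break-even R² is only about 0.005 and the value is already collected. The result rests on the assumed R², on 5.5 being the residual SD before the term is added, and on a similar R² at both stages.

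**What to change.** Add time since stroke as a continuous fixed effect, for example log months, to the primary linear model at both interim and final analysis. Add it also to the continuous secondary models that reuse that model. A continuous term uses the whole 6-month to 10-year range, which the 12-month split does not.

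Settle this in the statistical analysis plan before the trial statisticians access unblinded data. The Blinding section keeps them blinded throughout, so this is possible in principle. Leave the minimisation and the 0.792 and 2.176 bounds as they are. If the interim analysis has already been run, keep the current primary model and prespecify the extended one as a sensitivity analysis.

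The cost is one line of text, one degree of freedom, and a model with one more term than the minimisation factors. No new data are needed.
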